### Maternal metabolic associations with newborn phenotypes

Maternal prepregnancy obesity can predict higher branched chain amino acids and related metabolites in offspring.^51^ The increase in maternal prepregnancy BMI is strongly associated with adverse cardiometabolic profile (very low-density lipoprotein [VLDL], VLDL-cholesterol, VLDL-triglycerides, VLDL-diameter, branched/aromatic amino acids, glycoprotein acetyls and triglycerides) in offspring.^52^ A Mendelian randomisation study has suggested causal relationships between genetically elevated maternal prepregnancy BMI (1 SD) and blood glucose levels (7.2 mg/dL) with higher birth weight (55 g [95% CI: 93 g; p=0.004] and 114 g [95% CI: 147 g; p=7×10^–9^], respectively) of the offspring.^53^ The metabolic shift from first to third trimester of gestation can influence newborn phenotypes. A large study related to the effects of maternal metabolic signatures on fetal growth has identified urinary metabolites (like branched-chain amino acids, isoleucine, valine, leucine, alanine, choline, 3-hydroxyisobutyrate, progesterone and oestrogens) predictive of fetal growth, and explained 48%–53% of total variation in birth weight.^16^ Recently, a pilot study has shown that both gestational age of the pregnancy (comparable to that estimated by ultrasound) and risk for preterm delivery can be predicted by measuring cell-free RNA transcripts in maternal blood during pregnancy.^54^ This study highlighted the opportunities offered in the identification of non-invasive blood-based biomarkers of pregnancy outcome.^54^ It has been shown that maternal hyperglycaemia is associated with higher cord blood concentrations of lysophosphatidylcholines in offspring independent of lifestyle intervention among obese women.^55^ Thus, maternal prepregnancy BMI, RNA transcripts and hyperglycaemia during gestation influences fetal and newborn phenotypes.

Scholtens *et al*
56 assessed the impact of maternal hyperglycaemia, measured using an oral glucose tolerance test (OGTT), on fetal phenotypes at 28 weeks of gestation. They observed a decrease in amino acids, fatty acids and products of lipid metabolism, whereas a rise in triglycerides and carbohydrates was observed between fasting and 1 hour OGTT samples. Furthermore, the role of maternal glucose, triglycerides and fatty acids in predicting the newborn birth weight and sum of skinfolds thicknesses was also suggested. This confirmed the Freinkel modification of the Pedersen hypothesis, that is, fetal growth and fat accumulation in the setting of maternal hyperglycaemia is contributed to by other nutrients in addition to glucose.^57^ The longitudinal assessment of the role of maternal metabolites during the length of the pregnancy on birth outcomes is restricted to four studies, of which two studies use urine samples^16 58^ and the remaining two blood samples.^15 17^

### Gestational route to healthy birth cohort study

GWG in first trimester acts as an exposure for the levels of metabolites as an outcome in subsequent trimesters. Similarly, the levels of metabolites in a trimester can also act as an exposure for GWG in next trimester(s). Therefore, this study aims to quantify differential metabolic variability in relation to maternal weight gain during pregnancy for assessing its influence, as an exposure, on a) fetal growth, b) offspring metabolite levels, c) body composition of offspring at birth. The conceptual model is given in figure 1. We are asking two research questions:

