**Ethics and dissemination:**

The study has been approved by the ethics committees of the Department of Anthropology, University of Delhi and Sardar Patel Medical College, Rajasthan. We are taking written informed consent after discussing the various aspects of the study with the participants in the local language.

Strength and limitations of this studyThis is a longitudinal study in India to examine trimester-specific metabolomic changes during the course of pregnancy and their influence on fetal growth.The study is collecting biological measurements on pregnant women during each trimester (first, second and third trimester) and their offspring at the time of birth.Newborns will be intensively phenotyped for the levels of metabolites and body composition.Unlike other Indian cohorts, the study participants are being recruited from a government hospital that caters for a rural population.Lack of information on prepregnancy measurements will restrict our analysis to the duration of pregnancy only.

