### Study objectives

To detect differential changes in quantitative metabolites between the end of the first, second and third trimesters of pregnancy and to examine how these trajectories are associated with maternal weight gain.To determine the influence of metabolic changes during pregnancy on fetal growth, body composition (fat mass, lean mass and bone density) and anthropometry at birth (ie, body length, weight and circumferences) independent of maternal prepregnancy BMI and paternal phenotypic characteristics.To assess the association between maternal metabolic profile during pregnancy and metabolite levels of offspring at birth (in cord blood).

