### Questionnaires

A comprehensive questionnaire has been developed for collecting information on demographic, anthropological (caste, religion and consanguinity), medical disease history, tobacco and alcohol intake and passive smoking. The validated food frequency questionnaire of '*Indian Migration Study'* is being used for evaluating dietary intake.^79^ Maternal physical activity during pregnancy is being assessed using the international physical activity questionnaire (ie, 7 days long).^80–82^ The assets-based tool of National Family Health Survey-4 is being used to evaluate socioeconomic position.^83^ For assessing depression, we are using the Patient Health Questionnaire^84^ and Edinburgh Postnatal Depression scale.^85^ The WHO-5 questionnaire is being used for collecting information on quality of life.^86^ The capability well-being, that is, individual’s freedom to function in five key areas of their life: ’stability', ’attachment', ’achievement', ’autonomy' and ’enjoyment', is being assessed by using the ICEpop CAPability measure for Adults.^87–89^ Information on maternal environment, gynaecological and obstetrics history is also being collected using tools adapted from INTERGROWTH study.^90 91^ Additionally, a structured questionnaire on social factors like relationships with family members, husband position in household, social support during pregnancy and travel is being used for assessing the quality of social life and adequacy of social support (table 1).

**Table 1 T1:** Measures, tools and time points of data collection

	Mother			Offspring
	First trimester	Second trimester	Third trimester	
Timing of data collection	10th to 13th weeks	22nd to 24th weeks	32nd to 34th weeks	Birth
Gynaecological and obstetric	✔	✔	✔	–
Socioeconomic position	✔	✔	✔	–
Anthropological (caste and religion)	✔	✔	✔	–
Education	✔	✔	✔	–
Marital status	✔	✔	✔	–
Smoking	✔	✔	✔	–
Alcohol drinking	✔	✔	✔	–
Medication	✔	✔	✔	–
Disease history	✔	✔	✔	–
Maternal environment	✔	✔	✔	–
Physical activity (IPAQ)	✔	✔	✔	–
Time-activity pattern	✔	✔	✔	–
Food frequency	✔	✔	✔	–
Dietary recall (3 days)	✔	✔	✔	–
PHQ-12	✔	✔	✔	–
Well-being (WHO-5)	✔	✔	✔	–
Depression (EPNDS)	✔	✔	✔	–
Social factors	✔	✔	✔	–
Capability well-being (ICECAP-A)	✔	✔	✔	–
Anthropometry				
Height/body length	✔	✔	✔	✔
Sitting height	✔	✔	✔	–
Weight	✔	✔	✔	✔
Circumferences	✔	✔	✔	✔
Skinfolds	✔	✔	✔	✔
Blood pressure	✔	✔	✔	–
Laboratory tests: Glucose, insulin, Hb, lipids, LFT and KFT and blood group	✔	✔	✔	✔
Metabolomic data	✔	✔	✔	✔

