### Data analyses

The evaluation of cross-sectional associations of maternal body weight with quantitative metabolite levels in each trimester, independently, will be done using regression-based modelling. Both level of metabolites and gestational weight in each trimester will act as exposure as well as outcome. Variables like socioeconomic position, gestational age, parity, diet, smoking and physical activity will be considered as confounders. Maternal characteristics will be considered as exposures (like trimester-specific weight, metabolite levels) to evaluate their association with offspring-related outcomes (fetal growth, birth weight, body compositions and metabolite levels). The potential confounders for maternal-offspring associations will be socioeconomic position, gestational age, parity, diet, sex of the offspring, smoking and physical activity.

Mixed effects regression models for repeated measures will be applied for examining longitudinal associations of weight gain from first to third trimester^42^ with maternal levels of metabolites during pregnancy and fetal growth.^105^ We will also analyse the associations of level of metabolites from first to third trimester with trajectories of GWG. Mediation analyses will be conducted for evaluating the role of maternal metabolites as intermediates between GWG and offspring’s body composition.^106^ False discovery rate based multiple testing correction for number of metabolites will be applied.^107^ Mediation analysis will be conducted to examine whether the effect of GWG on fetal growth is mediated through alteration in levels of circulating metabolites.

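### Weight gain within the first trimester is named as an exposure, but only one first-trimester weight is planned and no prepregnancy weight exists, so it cannot be computed

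*Protocol article*

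**What the plan says.** The section that introduces the cohort says that "GWG in first trimester acts as an exposure for the levels of metabolites as an outcome in subsequent trimesters", adds that metabolite levels in one trimester may in turn act on later gain, and derives the study aim from these two statements.

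Objective 1 (Study objectives) sets the time points: "between the end of the first, second and third trimesters of pregnancy and to examine how these trajectories are associated with maternal weight gain". Objective 2 asks for effects that are independent of the mother's prepregnancy BMI.

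Table 1 (under Questionnaires) gives the timing of maternal weight and metabolomic data: "10th to 13th weeks", "22nd to 24th weeks" and "32nd to 34th weeks", one visit per trimester. Its birth column belongs to the offspring and contains no maternal weight.

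The strengths and limitations list after the abstract says: "Lack of information on prepregnancy measurements will restrict our analysis to the duration of pregnancy only".

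The Data analyses section plans mixed effects models for "examining longitudinal associations of weight gain from first to third trimester". It also treats trimester-specific weight as an exposure and lists gestational age among the confounders.

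**The concern.** Gain over an interval is a difference between two weights that bracket it. For the first trimester the plan supplies only the later one. Without an earlier weight, no model can recover the gain.

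This matters because early gain carries much of the rationale. The introduction cites work on gain in the first 14 weeks and on early fat deposition that may alter metabolites later in pregnancy. That process begins before the first weighing. If the hypothesis stays as worded, the nearest available stand-in is attained weight at 10 to 13 weeks. That weight largely reflects body size rather than gain, and a finding based on it could be read as evidence about early gain.

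Objective 2 has the same gap: prepregnancy BMI needs a weight that the article says is not available.

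**Working it through.** The article states no figure for this quantity, so there is none to reproduce. The check is whether each named quantity can be formed from the planned weights.

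**Inputs (Table 1).** Maternal weight at visit 1, weeks 10–13; visit 2, weeks 22–24; visit 3, weeks 32–34. Prepregnancy weight: none (strengths and limitations list).

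**Step 1: gain within the first trimester.** Two weights are needed and one is planned. Not computable. The eligibility list mentions 10 weeks of gestation, possibly with a comparison sign lost in extraction. Earlier recruitment would not help, because Table 1 still schedules only one first-trimester weight.

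**Step 2: gain between visits.** Shortest interval = earliest week of the later visit minus latest week of the earlier visit. Longest interval = latest week of the later visit minus earliest week of the earlier visit.

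| Interval | Shortest | Longest |
|---|---|---|
| Visit 1 to 2 | 22 − 13 = 9 weeks | 24 − 10 = 14 weeks |
| Visit 2 to 3 | 32 − 24 = 8 weeks | 34 − 22 = 12 weeks |
| Visit 1 to 3 | 32 − 13 = 19 weeks | 34 − 10 = 24 weeks |

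All three are computable. Gain before visit 1 and after visit 3 is not observed.

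**Step 3: time order.** With gain from visit 1 to 2 as the exposure, the maternal metabolite measurement that follows it is visit 3; visit 2 coincides with the end of the exposure interval. In the reverse direction, visit-1 metabolites do precede gain from visit 1 to 2, so that half of the cohort section's statement can be studied.

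**Step 4: trimester ends.** The article does not define them. Assuming ends at about weeks 13–14, 26–28 and 37–40, the distance from visit to trimester end is:
- first: 13 − 13 = 0 to 14 − 10 = 4 weeks
- second: 26 − 24 = 2 to 28 − 22 = 6 weeks
- third: 37 − 34 = 3 to 40 − 32 = 8 weeks

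The first window roughly reaches the trimester end; the other two do not, under this assumption.

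**Step 5: effect of scheduling on gain in kg, visit 1 to 3.** The interval varies by 24 − 19 = 5 weeks. The rate is assumed to be 0.3 to 0.5 kg/week. The upper value is the cut-off for excessive gain that the introduction cites from other studies; the lower is an assumption.
- Extreme contrast: 5 × 0.3 = 1.5 kg to 5 × 0.5 = 2.5 kg.
- With independent uniform attendance over windows 3 weeks (10 to 13) and 2 weeks (32 to 34) wide, SD of the interval = √((3² + 2²)/12) = √(13/12) = 1.04 weeks, which is 1.04 × 0.3 = 0.31 kg to 1.04 × 0.5 = 0.52 kg.

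**The case against.** The strongest reply is that the sentence on first-trimester gain is conceptual background. The aim in the same section, the research questions and objective 1 speak of weight gain during pregnancy, and the Data analyses section uses gain from first to third trimester and trimester-specific weight. All of these can be formed from the three visits. The article also discloses that prepregnancy data are lacking and narrows its analysis accordingly. This stands, and it limits the reach of the point. It does not remove it: the sentence names an exposure and leads directly into the aim, and the disclosure confirms that the exposure has no starting value.

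Four stronger readings are tempting and are not supported:

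- A reader might infer that the main weight-gain analysis fails. It does not; gain from visit 1 to visit 3 serves the planned mixed models.
- A reader might infer that gain up to delivery is planned and that its last weeks will be lost. The abstract mentions follow-up at delivery, but no analysis of gain to delivery is proposed. The unobserved late weeks limit interpretation and are not a broken analysis.
- A reader might infer that objective 1 cannot be carried out because the visits are not at trimester ends. The mismatch rests on conventional definitions that the article does not give, and changes between the actual visits can be computed. This is loose wording.
- A reader might infer that variable visit timing will distort the results. Nothing says that untimed gain in kg will be used. Each pregnancy is dated from the last menstrual period with an ultrasound check, and gestational age is a listed confounder, so adjustment may absorb part of the effect.

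**Conclusion.** The point holds in a limited form and is wrong as written. Gain within the first trimester cannot be computed from the planned data, and this rests on the article's own text without any outside figure. The observable exposures are gain from visit 1 to 2 and from visit 2 to 3, or their sum; conclusions can reach only from about weeks 10–13 to weeks 32–34. Objective 2's independence from prepregnancy BMI conflicts with the stated lack of prepregnancy measurements for the same reason.

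The trimester-end wording is a lesser mismatch that depends on assumed trimester definitions. Scheduling is secondary: at most 1.5 to 2.5 kg between extreme attenders and an SD of about 0.3 to 0.5 kg, given an assumed 0.3 to 0.5 kg/week and uniform attendance, before any adjustment for gestational age.

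**What to change.** 1. Remove first-trimester gain as an exposure, or name a source of an early or prepregnancy weight and say how reliable it is.
2. Define gestational weight gain as kg per week between dated visits (1 to 2 and 2 to 3), using gestational age at each visit. State that gain from first to third trimester means visit 1 to visit 3.
3. Enter visit-1 weight or BMI as a separate baseline covariate and do not label it gain.
4. In objective 1, replace the reference to trimester ends with the visit windows of Table 1.
5. In objective 2, reconcile the prepregnancy BMI adjustment with the stated limitation: either name the source of that BMI or substitute visit-1 BMI and say so.
6. Limit conclusions to gain between about weeks 10–13 and 32–34.

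Apart from any outside source of early weight, this uses measurements already planned. The cost is wording in the protocol and analysis plan and a narrower claim: the study would no longer speak to gain in early pregnancy.

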**Figure 1 F1:**
[figure not shown]
Diagrammatic representation of the study hypothesis. We assume that the quantitative changes in maternal circulating metabolites are associated with gestational weight gain, and it influences fetal growth, offspring’s levels of metabolites, and body composition and anthropometric traits at birth.

Are quantitative changes in levels of metabolites associated with GWG during pregnancy?Are quantitative metabolic changes during pregnancy associated with fetal growth, offspring levels of metabolites and body composition at birth?

### Study objectives

To detect differential changes in quantitative metabolites between the end of the first, second and third trimesters of pregnancy and to examine how these trajectories are associated with maternal weight gain.To determine the influence of metabolic changes during pregnancy on fetal growth, body composition (fat mass, lean mass and bone density) and anthropometry at birth (ie, body length, weight and circumferences) independent of maternal prepregnancy BMI and paternal phenotypic characteristics.To assess the association between maternal metabolic profile during pregnancy and metabolite levels of offspring at birth (in cord blood).

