**Methods and analysis:**

A prospective longitudinal study is planned (start date: February 2018; end date: March 2023) on pregnant women that are being recruited in the first trimester and followed in subsequent trimesters and at the time of delivery (total 3 follow-ups). The study is being conducted in a hospital located in Bikaner district (66% rural population), Rajasthan, India. The estimated sample size is of 1000 mother-offspring pairs. Information on gynaecological and obstetric history, socioeconomic position, diet, physical activity, tobacco and alcohol consumption, depression, anthropometric measurements and blood samples is being collected for metabolic assays in each trimester using standardised methods. Mixed effects regression models will be used to assess the role of gestational weight in influencing metabolite levels in each trimester. The association of maternal levels of metabolites with fetal growth, offspring’s weight and body composition at birth will be investigated using regression modelling.

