### Recruitment strategy

Women visiting the antenatal clinic of the PBM hospital are being screened with the help of a one-page questionnaire to assess their eligibility for the study. We aim to screen around 6000 pregnant women from PBM hospital to reach the targeted sample size. The participants will have to satisfy the eligibility criteria (given below) before being recruited at baseline (figure 2) from February 2018 to March 2023:

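### Neither confounder list names season or visit date, so a yearly cycle shared by weight gain, metabolites and birth outcomes could bias their associations, although it largely cancels in the mean trimester change

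*Protocol article*

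**What the plan says.** Under Study objectives, the first objective has two parts. One is "To detect differential changes in quantitative metabolites between the end of the first, second and third trimesters of pregnancy". The other links the resulting trajectories to the mother's weight gain. The second and third objectives relate maternal metabolites to fetal growth, body composition and anthropometry at birth, and to cord-blood metabolites.

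Table 1 (Questionnaires) sets the first visit at weeks 10 to 13, the second at weeks 22 to 24 and the third at "32nd to 34th weeks". Under Recruitment strategy, women must meet the eligibility criteria "before being recruited at baseline (figure 2) from February 2018 to March 2023". The abstract gives the same two dates as the start and end of the study.

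Data analyses has two confounder lists. The maternal one reads "Variables like socioeconomic position, gestational age, parity, diet, smoking and physical activity will be considered as confounders". The mother-to-child one reads "The potential confounders for maternal-offspring associations will be socioeconomic position, gestational age, parity, diet, sex of the offspring, smoking and physical activity". Gestational age is the only time variable in either list. The maternal list is open-ended. The maternal-offspring list is a specific enumeration, though of potential confounders.

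**The concern.** The first and third visits fall nearly half a year apart. If a metabolite has a yearly cycle, through food supply, temperature, activity or infection, part of a woman's change between these visits is seasonal and not gestational. Women who conceive in the same month share that shift. If weight gain also has a yearly cycle, season is a common cause of both, and the regression of one on the other picks it up.

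The maternal-offspring associations have the same structure. Conception date largely fixes the season of each maternal sample, of birth and of cord-blood collection. The planned mediation analyses (weight gain, metabolites, offspring outcome) could be affected too, since season could act on all three.

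Gestational age cannot stand in for season. Each visit has a narrow gestational window while enrolment covers every month, so two women at the same gestational age can be sampled in opposite seasons. Diet and physical activity would carry only part of a seasonal effect.

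**Working it through.** The article states no figure for season, so there is nothing to reproduce first. The check has four steps.

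**1. Gap between visits (Table 1).** Shortest: 32 − 13 = 19 weeks. Longest: 34 − 10 = 24 weeks. Between midpoints: 33 − 11.5 = 21.5 weeks.

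**2. Seasonal part of one woman's change.** Take one annual sine wave of amplitude A (peak-to-trough swing 2A) and a year of 52.18 weeks. For a gap of d weeks, the seasonal difference is 2A × s × cos(phase), where s = sin(πd/52.18) and the phase depends on the enrolment date.

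| Gap (weeks) | s = maximum share of the swing | Mean absolute share = s × 2/π |
|---|---|---|
| 19 | 0.91 | 0.58 |
| 21.5 | 0.96 | 0.61 |
| 24 | 0.99 | 0.63 |

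At 21.5 weeks, 23% of enrolment dates give more than 90% of the swing, 35% give less than half, and the signed mean over a full year is zero.

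**3. Mean trimester change.** February 2018 to March 2023 is about 62 months, or T = 5.17 years. With uniform enrolment, the worst-phase bias as a share of the swing is s × |sin(πT)|/(πT) = 0.962 × 0.5/16.23 = 0.03. Over exactly 60 months it is 0. If enrolment stopped about seven months early to allow for delivery (55 months), it is 0.06. If the enrolment rate itself varied over the year by ±20% or ±50% (an assumption), the worst case is s × 0.2/2 = 0.10 or s × 0.5/2 = 0.24 of the swing.

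**4. Association of weight gain with metabolite change.** Let weight gain have a yearly cycle of amplitude B, in units of its own SD. Under uniform enrolment, the seasonal covariance with metabolite change is 0.5 × B × 2As × cos(phase difference). It is zero only if the two cycles are a quarter of a year apart, and a larger sample does not shrink it.

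Assumptions, none of them in the article: A and B between 0.1 and 0.3 SD, within-woman correlation ρ of 0.5 to 0.6, cycles exactly in phase, gap 21.5 weeks (2s = 1.92).

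- Variance of change = 2(1 − ρ) + (1.92A)²/2.
- Low end (A = B = 0.1, ρ = 0.5): variance = 1 + 0.018 = 1.018; r = 0.5 × 0.1 × 0.192/√1.018 = 0.01.
- High end (A = B = 0.3, ρ = 0.6): variance = 0.8 + 0.166 = 0.966; r = 0.5 × 0.3 × 0.576/√0.966 = 0.09. With ρ = 0.5 it is 0.08.
- Season's share of the variance of change: 0.018/1.018 = 2% to 0.166/0.966 = 17%.

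The nearest benchmark is the Sample size section, where maternal weight is to explain 4%-5% of the variation in a metabolite: r = √0.04 = 0.20 to √0.05 = 0.22. That target is for a cross-sectional analysis. In explained variance, the worst case is 0.09² = 0.8% against 4%-5%.

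The same covariance formula applies to the second and third objectives, with a seasonal amplitude for the offspring measure in place of B. I have put no figure on those.

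**The case against.** The strongest reply is that the article does not exclude season. The maternal list, which governs the first objective, opens with wording that makes it illustrative, and the maternal-offspring list speaks only of potential confounders. A journal article condenses a fuller plan, and date terms may appear there. Diet and physical activity are measured at every trimester visit and adjusted for, which removes part of any seasonal effect acting through them. Nothing in the article shows that season affects these metabolites or weight gain in this population, and the worst case needs both assumed amplitudes at their maximum and the cycles in phase.

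Most of this stands. It rules out saying that every model will omit calendar time; the text supports only that neither list names it. It does not remove the point. A list specific enough to name sex of the offspring has no calendar term, the listed covariates are partial proxies, and the remedy is concrete and nearly free.

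A reader might also infer that each woman's change carries nearly the full seasonal swing. That is the maximum over enrolment dates; some women carry almost none. A reader might infer that season is systematically mixed with trimester in the mean contrast. That needs uneven enrolment over the year, which the article does not indicate.

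**Conclusion.** The point holds as a limited one. Over about five years of roughly even enrolment, a yearly cycle leaves at most a small bias in the mean trimester change (about 3% of the swing at worst phase over 62 months) and mainly adds between-woman variance. In the associations that make up the rest of the objectives, it does not cancel if season acts on both sides.

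Under the stated assumptions, the spurious correlation of weight gain with metabolite change is about 0.01-0.09. At most this is well under half of the 0.20-0.22 implied by the 4%-5% target. The size rests wholly on assumed amplitudes and could be nil.

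Two stronger readings of the size are not supported. The 2% explained variation in the Sample size section (r about 0.14) is the target for fetal growth predicted from metabolites, so it is the wrong yardstick for weight gain. A false-positive rate at α = 0.0001 would not describe the planned decisions, because Data analyses specifies a false discovery rate correction.

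**What to change.** Under Data analyses, add calendar time to both confounder sets:

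- **Maternal regressions and mixed models:** sine and cosine of visit date with a one-year period, entered as time-varying terms, plus calendar year. Report the trimester contrasts and weight-gain associations of the first objective from these models.
- **Maternal-offspring models:** sine and cosine of estimated conception date, plus calendar year.

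Because enrolment spans several years, trimester and season can be separated. The cost is about 3 degrees of freedom with linear year (2 + 1), or about 7 with categorical year over 2018-2023 (2 + 5), out of about 1000 women. No new data are needed: computing gestational age as described under Estimation of gestational age already requires these dates.
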